### Secondary outcome measure

2.11

**Symptoms scores**. Measured by CAT and mMRC scores. Patients will be required to complete assessments every day during hospitalization.

**Lung function**. Lung function indicators include FEV1, FEV1/FVC, and FEV1%. These will be compared before and after treatment.

**Exercise tolerance**. We will assess each patient's exercise endurance using 6MWD. Method: hospitalized patients will be asked to walk as far as possible within 6 min along flat ground once a day. For the standardized instructions of 6MWD, we will refer to the official European Respiratory Society/American Thoracic Society technical standard for field walking tests in chronic respiratory disease.^[18]^

**Inflammatory indicators**. Include CRP and PCT. We will collect the results of CRP and PCT in admissions and discharges.

**Length of hospital stay** Length of hospital stay = discharge date – admission date + 1.

**Symptoms and quality of life scores during the follow up.** Patients will be followed up by phone every week to produce the CAT, mMRC, and 6MWD scores for 12 weeks after discharge.

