### Length of intervention time

2.7

The entire hospital stay will be ∼7 to 14 days.

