### Discharge criteria

2.8

The theoretical discharge criteria will be^[8]^:

1.Clinicians believe that patients can adapt to home medical care;2.Patients can use long-acting bronchodilators, such as β2 receptor agonists and anticholinergics, with or without inhaled glucocorticoids for stable inhalation therapy. Inhaled short-acting β2 receptor agonists should be administered less than once every 4 h;3.If the patient is not bedridden, they need to be able to walk indoors;4.Patient is able to eat and sleep and is not affected by dyspnea;5.Patient clinically stable for 12 to 24 h;6.Arterial blood gas analysis is stable for 12 to 24 h;7.The patient (or family member) fully understands the proper use of the drug in the stable phase;8.Follow-up and care plans are properly arranged (e.g., follow-up to community doctors and family medicine).

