### Follow up

2.9

Patients will be followed up by phone once a week for 12 weeks after discharge. The contents of the follow up mainly included the scores of CAT, mMRC, and 6MWD.

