### Study procedures

2.14

Eligible subjects will be screened 2 days before the trial. Randomized group treatment will be conducted after informed consent is obtained and baseline information is collected. The duration of the intervention will be the entire hospital stay (7–14 days). All hospitalized patients will complete the CAT, mMRC, and 6MWD scales every day. The physician should record each patient's glucocorticoid dosage every day and make corresponding adjustments according to the CAT scores. The patients will be asked about their symptoms and quality of life scores (assessed by CAT, mMRC, and 6MWD) after discharge for 12 weeks by weekly telephone follow-up. The spirit figure of enrollments, interventions, and assessments is presented in Figure 2.^[15]^

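### After about day 7 no CAT or mMRC reading is scheduled on a common day from randomisation for all patients, so later symptom comparisons would depend on a recovery-driven discharge and tend to understate a real benefit

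*Protocol article*

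**What the plan says.** Section 2.11 (Secondary outcome measure) makes CAT and mMRC the symptom outcome and states: "Patients will be required to complete assessments every day during hospitalization". Section 2.14 (Study procedures) agrees: "All hospitalized patients will complete the CAT, mMRC, and 6MWD scales every day".

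The in-hospital period differs between patients. Section 2.7 says "The entire hospital stay will be ∼7 to 14 days". Section 2.8 lists eight discharge criteria. Several describe recovery, among them "Patient clinically stable for 12 to 24 h" and "Patient is able to eat and sleep and is not affected by dyspnea".

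After discharge the schedule changes. Section 2.9 says "Patients will be followed up by phone once a week for 12 weeks after discharge", and sections 2.11 and 2.14 repeat the discharge-based timing.

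Length of stay is itself a secondary outcome in section 2.11: "Length of hospital stay = discharge date – admission date + 1". Section 2.16 names the t test and the Wilcoxon rank-sum test for continuous data. It does not say on which day symptom scores will be compared.

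**The concern.** Whether a patient has a score on a given day between day 8 and day 14 depends on whether that patient has recovered enough to go home, and the score measures much the same recovery. If the TCM granules speed recovery, the TCM arm loses its recovered patients sooner, and those still in hospital are a smaller and more selected group of slow recoverers than in the placebo arm.

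The two obvious alternatives have related weaknesses. Scores at discharge are pulled together because patients leave in a similar state. Scores by week since discharge are taken earlier after randomisation in the arm that goes home sooner.

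All three comparisons therefore condition on a post-randomisation event that treatment may affect, and each tends to hide part of a real benefit. Because the data-collection schedule causes this, a later analysis plan cannot supply the missing same-day readings.

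**Working it through.** **1. The schedule set out by discharge day (sections 2.7, 2.9, 2.14).** A patient discharged on day D has daily scores to day D, then calls on days D+7, D+14 and so on. For simplicity, days are counted from a common start.

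| Discharge day D | Daily scores end | First call | Second call |
|---|---|---|---|
| 7 | 7 | 14 | 21 |
| 10 | 10 | 17 | 24 |
| 14 | 14 | 21 | 28 |

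Day 7 is the last day on which everyone is scheduled to be scored.

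**2. Coverage.** Assume discharge is spread evenly over the eight days 7 to 14 (not in the documents). The share still scored daily on day d is (15 − d)/8:
- day 10: 5/8 = 62.5%
- day 12: 3/8 = 37.5%
- day 14: 1/8 = 12.5%

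**3. Size if discharge follows CAT closely.** The document states no figure to reproduce, and every input here is an assumption:
- admission CAT has mean 25 and SD 5;
- CAT on day t is B(1 − r·t), where B is the admission score and r averages 5.5% per day (TCM) or 4.8% (placebo), with SD 1.5 percentage points between patients;
- discharge is on day ceil(0.5/r), held within days 7 to 14. The 50% threshold is borrowed from the primary outcome, not from section 2.8.

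Mean stay is then 10.0 versus 11.0 days. A hand check of the all-patient difference on day 10 gives 25 × (0.055 − 0.048) × 10 = 1.75 points. The day-10 difference among remaining inpatients is −0.75. The all-patient difference depends on what CAT does after discharge:

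| CAT after discharge (assumed) | All patients, day 10 | Inpatients, day 10 | Share kept |
|---|---|---|---|
| keeps falling linearly | −1.74 | −0.75 | 0.75/1.74 = 43% |
| improvement capped at 70% | −1.55 | −0.75 | 0.75/1.55 = 48% |
| held at discharge level | −1.02 | −0.75 | 0.75/1.02 = 74% |

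The difference in the last in-hospital score is −0.53. On calls by week since discharge, the TCM arm is reached on average 11.0 − 10.0 = 1.0 day earlier.

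**4. A second model with different assumptions.** Here admission CAT is 24 (SD 5), daily noise has SD 2, decline is exponential, and TCM recovery is 1.3 times as fast. Discharge is on the first day from day 7 with 50% improvement, at latest day 14.

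| Day | All patients | Inpatients | Share kept |
|---|---|---|---|
| 7 | −1.71 | −1.69 | 99% |
| 8 | −1.84 | −1.40 | 76% |
| 10 | −2.03 | −1.05 | 52% |
| 14 | −2.18 | −0.62 | 28% |

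Discharge at CAT ≤ 12 instead gives 72%, 55% and 39% on days 8, 10 and 14.

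**5. Where the effect weakens or disappears.**
- With no true effect, the inpatient difference stays at about 0.
- With discharge unrelated to recovery, it is −2.03 against −2.02 on day 10, so nothing is lost.
- Adding random variation of SD 2 days to discharge in the model of step 3 moves the day-10 inpatient difference from −0.75 to −1.20. That keeps 1.20/1.74 = 69% under linear decline; with CAT held after discharge, the loss disappears.

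**The case against.** **No faulty analysis is written down.** A reader might infer that the trial plans to compare remaining inpatients day by day. It does not say so. The daily CAT also serves the primary outcome and dose recording (sections 2.10 and 2.14), and the compared day may stand in an analysis plan that is not shown. This stands, so the point is about what is collected and is conditional on how it is used.

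**A longitudinal model could recover much of the loss.** A random-slope mixed model fitted to inpatient scores alone, under the inputs of step 3 (800 per arm, three runs), gave day-10 differences of −1.74, −1.86 and −1.94 against a true value of about −1.75. This stands in part. The model shared the linear form of the simulated data, and with real scores it would be extrapolating past discharge, when the granules have also stopped.

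**The discharge rule in the calculation is strict.** None of the eight criteria in section 2.8 is a CAT threshold, and some concern home care, blood gases or understanding of medication. This stands, and it is why the size is given as a range.

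**Later readings do sometimes coincide.** Patients discharged on days 7 and 14 are both due a call on day 21, and weekly calls put each patient within a few days of any chosen date. This stands: what is missing is one day shared by all patients.

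**Timing from discharge is legitimate for a post-discharge outcome, and length of stay captures faster recovery separately.** Both are true. They limit the importance of the point but do not give a same-day symptom comparison.

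**Conclusion.** The point holds as a feature of the schedule. After about day 7 there is no common-day CAT or mMRC reading for all randomised patients, and the three readily available later comparisons each depend on discharge. The likely direction is to understate a real benefit; no false benefit arises under the null. Early discharge because of deterioration could pull the other way.

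The documents do not give the size. On day 10, roughly 40 to 75% of the all-patient difference is kept if discharge closely follows CAT recovery, and more or all of it if discharge is noisier. A reader might infer that about half the effect is lost. That is not supported as a general figure, because it depends on an assumed discharge rule and on an assumed course of CAT after discharge.

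The point concerns a secondary outcome. It does not touch symptom scores to about day 7 or the primary endpoint. It is a low-cost improvement to the schedule, not a threat to the trial's main result.

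**What to change.** - **Sections 2.9 and 2.14:** collect CAT and mMRC from every randomised patient on day 7 and day 14 after randomisation, in hospital or by phone if already discharged. Time the later weekly calls from randomisation and continue them long enough to cover the stated 12 weeks after discharge.
- **Section 2.11:** name day 7 and day 14 after randomisation as the compared time points for the symptom outcome, in all randomised patients. Use the other inpatient scores descriptively, or in a longitudinal model that also includes the post-discharge scores.

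**Cost.** These are not quite the same calls on new dates. A day-7 call is extra for anyone already home. Twelve weekly calls starting on day 14 end on day 14 + 11 × 7 = 91, which is only 77 days (11 weeks) after a day-14 discharge. Covering 12 weeks for that patient means calling until day 14 + 84 = 98. Allow for one or two extra or re-dated calls per patient. Scores on day 14, and on day 7 for anyone already home, will mix in-person and phone collection, so the mode should be recorded. No treatment or discharge criterion needs to change.

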## Introduction

1

Chronic obstructive pulmonary disease (COPD) constitutes a group of diseases including small airway obstruction, emphysema, and chronic bronchitis. Chronic inflammation of the airway and lung parenchyma is the main feature of this disease, with progressive and irreversible airflow limitation.^[1]^ The main clinical manifestations are repeated cough, sputum, and dyspnea. It is usually caused by abnormal airways and alveoli caused by significant exposure to toxic particles or gases. The latest Global Initiative for Chronic Obstructive Lung Disease (GOLD) 2019 guidelines have added risk factors for COPD, such as indoor biofuels, socioeconomic status, human immunodeficiency virus infection, and genetic polymorphisms.^[2]^ Acute exacerbation of COPD (AECOPD) is defined as a sudden worsening of the main complaint (baseline dyspnea, cough, or sputum) in patients with COPD that exceeds normal day to day variations. Currently, the prevalence of COPD is on the rise. It is expected that more than 4.5 million people will die annually owing to COPD by 2030. Thus, COPD will become the third leading cause of death worldwide and a public health problem in every country.^[3,4]^

Airway inflammation is the most basic pathological change in COPD, especially in the acute exacerbation stage,^[5]^ which formed the theoretical foundation for glucocorticoid therapy. The systemic use of glucocorticoids, one of the major treatments for AECOPD,^[6]^ promotes symptom relief, shortens the course of AECOPD, reduces the length of hospital stay, and improves forced expiratory volume in 1 s (FEV1) values; however, the long-term use of steroid hormones causes muscle weakness, diabetes, osteoporosis, fluid retention, hypertension, adrenal depression,^[7]^ secondary infections (pneumocystis pneumoniae), seizures, insomnia, weight gain, anxiety, depressive symptoms, and many other significant adverse reactions.^[8]^ Each side effect is an independent risk factor for death.^[9]^ Therefore, clinicians are actively seeking safer alternative treatments that still benefit from the use of glucocorticoids.

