### Trial design and oversight

2.1

This will be a prospective, placebo-controlled clinical trial to evaluate the efficacy of TCM in the treatment of patients with AECOPD. A total of 204 eligible patients will be enrolled according to the exclusion and inclusion criteria and randomly assigned to the TCM or placebo group at a 1:1 ratio. The antibiotic group and non-antibiotic group will be set in advance for subgroup analysis. After a 7–14 day intervention and 12 weeks of follow up, the efficacy of TCM in the treatment of patients with AECOPD will be evaluated based on the primary endpoint (the dosage of systemic glucocorticoids [at which CAT scores improve by 50%]) and secondary endpoints (symptoms scores, exercise tolerance, lung function, length of hospital stay, symptoms, and quality of life scores during the follow up). The flow chart of the study is presented in Figure 1.

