### Randomization and intervention

2.6

The randomization protocol will be designed by a member of the Sichuan TCM Evidenced-Based Medicine Center. They will generate 204 random numbers will using SAS 9.2 statistical software (SAS Institute, Cary, NC). Treatment allocation will be conducted by an independent statistician according to the random numbers generated by the statistical software. Eligible patients will be randomly assigned to either the TCM group or the placebo group using sealed opaque envelops after obtaining informed consent. A special manager will record this randomization process. An individual's randomization number and group allocation can be identified by checking the envelope, which will be performed in case of a clinical emergency.

All participants will receive basic Western medical therapy advocated by the Chinese Expert Consensus on the diagnosis and treatment of AECOPD (2017 update),^[8]^ which includes:

1.Controlled oxygen therapy: Venturi mask inhales oxygen.2.Bronchodilators: compound ipratropium bromide solution for inhalation (Laboratoire Unither, Amiens, France), 2.5 mL, inhale, three times a day;3.Phlegm medicine: fudosteine tablets (Pharmaceutical Co., Ltd.), 0.4 mg, orally, three times a day;4.Glucocorticoids: methylprednisolone sodium succinate for injection (Tianjing Jinyao Pharmaceutical Co., Ltd. Tianjing, China), 40 mg, administered with 0.9% sodium chloride injection (100 mL), intravenously, once a day (depending on the patient's condition, the dosage can be reduced or changed to oral administration, but the longest course of treatment cannot exceed 14 days);5.Antibacterial drugs: according to bacterial resistance and the general course of treatment will be 5 to 7 days, although special circumstances can appropriately extend the application time of antibacterial drugs.

In addition, the TCM group will receive TCM granules (one bag at a time, three times a day) and the Placebo group will receive Placebo granules (one bag at a time, three times a day). Both groups will or will not receive antibiotic treatment according to the antibiotic treatment criteria, which are:

1.During AECOPD, aggravated difficulty breathing, increased sputum volume, and purulent sputum occur simultaneously;2.The patient only has two of the above three symptoms, but has purulent sputum;3.Severe acute exacerbation that requires invasive or noninvasive mechanical ventilation.

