### Statistical analysis

2.16

Intention-to-treat analysis and per-protocol analysis will be used. Intent-to-treat analysis means that after subjects are randomized, whether they choose to withdraw from the trial or switch to another group, their results are based on their initial grouping during data analysis. Intention-to-treat analysis will be used to analyze completed cases and dropout cases. Efficacy analysis adopts per-protocol analysis; thus, it kicks out those cases with insufficient compliance during the analysis and analyzes only the completed cases. When there is a difference between the two results, the difference will be discussed and explained.

We will use SPSS 19.0 statistical software for statistical analysis. The measured value of the data will be expressed as mean ± standard deviation. If the data follow the normal distribution and the variance is homogeneous, the *t* test will be used; however, if the data does not follow the normal distribution or the variance is uneven, the Wilcoxon rank-sum test will be sued. The Bonferroni method will be used to further compare the differences between antibiotic and non-antibiotic subgroups to explore whether antibiotics will affect the outcomes. The Chi-square test will be used for counting data and rank-sum test will be used for ranking data. All tests will be two-sided, with *P* < .05 being considered statistically significant.

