## Discussion

3

COPD has a “high morbidity and high mortality rate” worldwide, and has become a major problem for medical treatment. In particular, the acute deterioration of respiratory symptoms during the acute exacerbation period poses a serious threat to health and requires additional treatment. The 2019 GOLD guidelines state that the cause of the acute exacerbation of COPD is often respiratory infections and affirm the therapeutic role of systemic glucocorticoids in the acute phase: improving patient lung function, increasing oxygenation, and shortening hospitalization and recovery time.^[5]^ However, systemic glucocorticoids cause a variety of adverse reactions such as hyperglycemia, hypertension, osteoporosis and femoral head necrosis, and gastrointestinal bleeding and higher doses of glucocorticoids cause a higher risk of adverse reactions.^[19]^ Therefore, glucocorticoids have become a topic of concern. Whether TCM can reduce the dosage of glucocorticoids is worth research.

Currently, there are a small number of research reports on the efficacy of TCM for the reduction of the dosage of glucocorticoids in patients with AECOPD.^[20–22]^ However, these reports use small sample size and do not use the reduction in glucocorticoids dosage as the primary outcome indicator. There is no high-quality clinical evidence of randomized, blinded, and large samples. Thus, in this test, the reduction of glucocorticoids dosage will be regarded as the primary outcome to evaluate the effect of the TCM in reducing the dosage of glucocorticoids for the treatment of AECOPD.

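### Section 2.11 states only a before-versus-after comparison for lung function; it should state the contrast between TCM and placebo

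*Protocol article*

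**What the plan says.** Section 2.11 (Secondary outcome measure) lists FEV1, FEV1/FVC and FEV1% as the lung function endpoints. The only comparison it gives for them is: "These will be compared before and after treatment". No arm is named, and no other section states a contrast between TCM and placebo for lung function.

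Four other places bear on how to read that sentence:

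- Section 2.1 (Trial design and oversight): "This will be a prospective, placebo-controlled clinical trial to evaluate the efficacy of TCM". Allocation is 1:1, and lung function is among the secondary endpoints on which efficacy is to be judged.
- Section 2.6 (Randomization and intervention): "All participants will receive basic Western medical therapy advocated by the Chinese Expert Consensus". This therapy includes a bronchodilator, a mucolytic and systemic methylprednisolone.
- Section 1 (Introduction), on systemic glucocorticoids: "improves forced expiratory volume in 1 s (FEV1) values". Section 3 (Discussion) repeats the point, listing among their effects in the acute phase "improving patient lung function, increasing oxygenation, and shortening hospitalization and recovery time".
- Section 2.16 (Statistical analysis): measured data get a t test if they are normal with homogeneous variance; otherwise, "if the data does not follow the normal distribution or the variance is uneven, the Wilcoxon rank-sum test will be sued". It does not say whether the t test is paired or two-sample, and it names no paired rank test.

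**The concern.** A before-versus-after comparison has the null hypothesis that lung function does not change over the stay. The trial's question is whether TCM adds anything to background therapy, and its null hypothesis is that the arms do not differ. On the article's own account, the background steroid improves FEV1, so the first null is expected to fail in both arms even if the granules do nothing. A significant before-after result in the TCM arm would then say nothing about TCM.

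The sentence also does not fit the analysis section. A before-after comparison is paired, but the rank-sum test in section 2.16 is for independent samples. An analyst working from these two sections could run either a paired within-arm test or a two-sample between-arm test and claim to have followed the protocol. Only the between-arm test supports an efficacy conclusion.

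**Working it through.** **What the article gives.** It states no figure for lung function: no expected change, no SD and no power. There is therefore no lung function figure to reproduce. From section 2.5 I use only the number of patients per arm, 87 evaluable and 102 randomised, and from section 2.16 the two-sided 5% level. (The 87 itself does not follow from the inputs in section 2.5: the formula there, with pooled SD 32.0 mg and difference 256.7 − 187.6 = 69.1 mg, gives 2 × (1.960 + 0.842)² × 32.0² / 69.1² ≈ 3.4, or 4 per arm. That is a separate matter. The present point needs only the number of patients to be recruited.)

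**Assumption.** TCM has no effect, and both arms change by the same amount, d = mean change / SD of the change. Because the article gives no value, d is shown over a range.

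**Within-arm paired test.** The test statistic has a noncentral t distribution with n − 1 degrees of freedom and noncentrality d√n. With √87 = 9.327, the noncentrality is 1.87 at d = 0.2, 2.80 at 0.3, 3.73 at 0.4 and 4.66 at 0.5. With √102 = 10.100 it is 2.02, 3.03, 4.04 and 5.05. The probability of p < 0.05 in the TCM arm is:

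| Assumed d | n = 87 | n = 102 |
|---|---|---|
| 0.2 | 0.454 | 0.516 |
| 0.3 | 0.790 | 0.851 |
| 0.4 | 0.958 | 0.979 |
| 0.5 | 0.996 | 0.999 |

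The normal approximation agrees closely at n = 87 (0.46, 0.80 and 0.997 at d = 0.2, 0.3 and 0.5). It gives 0.15 at d = 0.1 and the nominal 0.05 at d = 0. By the same approximation, the d at which the probability reaches 80% is (1.960 + 0.842)/√n, which is 0.30 for 87 patients and 0.28 for 102.

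**Between-arm test.** The shared change cancels in the difference between arms, so the false-positive rate does not depend on d. A simulation of 5,000 trials at each of d = 0.2, 0.3, 0.5 and 0.8, with 87 per arm, gave:

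- within-arm paired test: 44.8%, 78.8%, 99.7% and 100% significant;
- two-sample t test of change between arms: 4.4% to 4.9%;
- rank-sum test of change between arms: 4.3% to 5.2%.

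**Consequence.** The two readings of the same protocol give very different error rates for a claim about TCM. A between-arm test, including one that uses the tests already named in section 2.16, holds its level. The literal before-after test does not, and how badly it fails depends on a recovery whose size the article does not state.

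**The case against.** The strongest reply is that the sentence only says when spirometry is done. Section 2.11 is a list of outcome measures, most neighbouring entries describe how or when a measure is taken, and the analysis rules are in section 2.16. That reading is possible. However, the entry for CRP and PCT describes timing with a verb of collection, while the lung function entry uses a verb of comparison and is the only entry in 2.11 that states a comparison at all.

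The second reply is that the rest of the article points to a between-arm analysis: the randomised placebo-controlled design, the definition of intention-to-treat by initial grouping, the equal-variance condition (which belongs to the two-sample t test) and the rank-sum fallback. This stands. A reader might infer that the placebo arm is unused for lung function, or that the result would be significant with an inert granule. The documents support neither. Nowhere does the article say that a within-arm p-value replaces the comparison of arms, and the chance of a spurious result depends on an unstated recovery (about 45% at 0.2 SD).

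A reader might also infer that the arms will be read side by side, with TCM significant and placebo not. The article does not propose this. If it were done, the chance rate with 87 per arm would be p(1 − p): 0.454 × 0.546 = 25% at d = 0.2, 0.790 × 0.210 = 17% at 0.3, 0.958 × 0.042 = 4% at 0.4 and 0.996 × 0.004 = 0.4% at 0.5. The benchmark for a one-direction between-arm claim is 2.5%, so this hazard fades when recovery is large.

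Third, a two-sample t or rank-sum test of change between randomised arms is valid, so not naming ANCOVA is no error. That also stands.

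Finally, a condensed article may leave the model for a secondary endpoint to a fuller document. That would excuse silence. Here the article does state a comparison, and taken literally it cannot answer the trial's question.

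**Conclusion.** The point holds as a defect of wording with a real consequence if the sentence is followed as written. The only contrast stated for FEV1, FEV1/FVC and FEV1% is before versus after, with no arm named. That contrast cannot separate TCM from recovery under therapy common to both arms, and it does not match the independent-samples tests in section 2.16, which suggest that a between-arm comparison was intended.

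The percentages rest on three assumptions: no TCM effect, the same mean change in both arms, and approximately normal changes. The size of the shared change is assumed throughout. The endpoint is secondary and the primary conclusion is not affected, so this should be corrected but does not threaten the trial as a whole.

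**What to change.** Replace the comparison sentence in section 2.11 with wording such as:

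> Post-treatment FEV1, FEV1/FVC and FEV1% will each be compared between the TCM and placebo groups by analysis of covariance, adjusting for the pre-treatment value of the same measure. The between-group difference and its 95% confidence interval will be reported. Within-group changes from before to after treatment are descriptive only and support no efficacy claim.

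Add analysis of covariance to the methods in section 2.16 so that the two sections agree. If the sponsor prefers to keep the tests already named there, a two-sample comparison of change between arms is also valid. ANCOVA is preferred for its precision.

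The cost is wording only. Section 2.13 (Safety assessment) already schedules pulmonary function before treatment and on discharge, so no new visits, data or patients are needed. Under section 2.1, a protocol amendment needs renewed ethics approval. The change should be made before any comparison by treatment group is seen.

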Treatment with syndrome differentiation is one of the characteristics of the traditional Chinese medicine (TCM) theoretical system, and it is advantageous in the treatment of COPD and has achieved significant effects. “Phlegm-heat congested lung” is one of the major features of COPD.^[10]^ The TCM for clearing heat and resolving phlegm often achieves good effects in the treatment of AECOPD,^[11]^ inhibits inflammatory reactions,^[12]^ reduces airway mucus hypersecretion,^[13]^ controls lung infection, and reduces the use of antibacterial drugs.^[14]^ Based on these effects, we intend to further study the heat-clearing and phlegm-resolving effects of TCM on the reduction of the dosage of systemic glucocorticoids. In this trial, the dosage of systemic glucocorticoids will be regarded as the primary endpoint. The secondary endpoints will include: symptom scores, assessed by the COPD assessment test (CAT) scores and modified medical research council dyspnea scale scores (mMRC); exercise tolerance, measured by 6 minute walking distance (6MWD); lung function, measured by forced expiratory volume in 1 second (FEV1), the ratio of forced expiratory volume in 1 second to forced vital capacity (FEV1/FVC), and FEV1 as a percentage of predicted value (FEV1%); inflammatory indicators, include C-reactive protein (CRP) and procalcitonin (PCT); length of hospital stay; and symptoms and quality of life scores during the follow-up. The efficacy of TCM in the treatment of AECOPD will be assessed by these indicators.

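### Follow-up 6MWD is to be collected by weekly phone call, but the only method the plan describes is a physical walk by inpatients

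*Protocol article*

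**What the plan says.** The Introduction lists exercise tolerance as a secondary endpoint with 6MWD as its measure, separate from the symptom scores (CAT and mMRC).

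Section 2.11 (Secondary outcome measure) gives the method under exercise tolerance: "hospitalized patients will be asked to walk as far as possible within 6 min along flat ground once a day". It adds: "For the standardized instructions of 6MWD, we will refer to the official European Respiratory Society/American Thoracic Society technical standard for field walking tests".

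Three sections describe what happens after discharge:

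- Section 2.9 (Follow up) sets the mode: "Patients will be followed up by phone once a week for 12 weeks after discharge". It then sets the content: "The contents of the follow up mainly included the scores of CAT, mMRC, and 6MWD".
- Section 2.11, under the follow-up symptom and quality-of-life outcome: "Patients will be followed up by phone every week to produce the CAT, mMRC, and 6MWD scores for 12 weeks after discharge".
- Section 2.14 (Study procedures) has patients asked about the same three measures "after discharge for 12 weeks by weekly telephone follow-up".

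For the hospital stay, Section 2.14 also says: "All hospitalized patients will complete the CAT, mMRC, and 6MWD scales every day".

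**The concern.** The plan handles a performance test as if it were a questionnaire. It calls 6MWD a scale in Section 2.14 and a score in Sections 2.9 and 2.11, in one list with CAT and mMRC. Those two ask for the patient's own rating, so a phone call can deliver them. A walking distance has to be walked, timed and measured, and a call can only pass on a figure obtained some other way.

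Section 2.1 makes the follow-up scores part of the efficacy evaluation. If the text is followed as written, a between-group result labelled 6MWD could be reported for the 12 weeks after discharge although the numbers behind it were not obtained by the test that gives 6MWD its meaning.

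**Working it through.** The plan states no figure on this point, so there is none to reproduce. The check sets the sections side by side and then counts the affected assessments.

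**Step 1. Method against mode of contact**

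| Item | In hospital | After discharge |
|---|---|---|
| Contact | Inpatient stay of about 7 to 14 days (2.7) | Weekly phone call for 12 weeks (2.9, 2.11, 2.14) |
| CAT, mMRC | Daily questionnaires (2.11, 2.14) | By phone, feasible |
| 6MWD | Daily walk on flat ground, cited field-walking standard (2.11) | By phone, no walking procedure described |

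The text describes no clinic visit, home visit, measured course, device or self-test procedure after discharge.

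**Step 2. Slip, omission or stated rule?** The mode (phone) and the content (CAT, mMRC, 6MWD) appear together in three sections. That makes a stray wording error unlikely. Nor is it merely detail left to a fuller document, because the article itself fixes both elements and the pair does not fit the only method it gives.

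**Step 3. What values could result?** Either the call records nothing for 6MWD, or it records a distance the patient estimates or measures alone, on an unknown course and without the standardized instructions. The first is missing. The second is a different quantity from the one defined in Section 2.11.

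**Step 4. Number of values affected**

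Inputs: 204 patients planned (2.1, 2.5), 12 weekly calls (2.9), 15% dropout allowance with 174 patients needed (2.5), three measures per call (2.9).

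- Maximum, no dropout: 204 × 12 = 2,448 values.
- With the planned dropout: 174 × 12 = 2,088 values, if dropouts contribute no follow-up values.
- Share of what each call collects: one of three measures.

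**Step 5. What is not affected**

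The primary endpoint is a glucocorticoid dosage tied to CAT improvement and does not use 6MWD. The in-hospital 6MWD has a stated method. Follow-up CAT and mMRC can be obtained by phone.

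**The case against.** The strongest reply is that the plan fixes only how values are reported and does not say how, or whether, the patient walks. A patient could do a timed walk at home and give the distance over the phone, and instructions for this could sit in a full protocol that the article condenses. This stands in part: it would be wrong to say that 6MWD cannot be measured at all after discharge. But the article names one method, for inpatients, and a walk reported from an unknown course does not meet it.

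Several stronger readings are tempting, and the article does not support them:

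- **That the plan specifies a supervised test.** Supervision is an inference from the inpatient setting. The text speaks only of standardized instructions and a cited standard.
- **That follow-up values will be compared with in-hospital values.** No section states that comparison. Section 2.11 files follow-up 6MWD under symptom and quality-of-life scores, apart from exercise tolerance.
- **That any difference between groups would be uninterpretable.** The trial is randomized with a placebo made to resemble the granules. Reporting error of similar size in both groups would add noise and weaken a contrast; nothing in the article shows that it would differ by group. What remains is that the contrast would be one of reported distances and not of the defined test.
- **That patients are told to make weekly maximal walks alone at home.** The plan does not say so. Section 2.14 has them asked about their scores.

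It is also fair to say that the count of values shows how far the problem reaches and does not show an effect on any conclusion.

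**Conclusion.** The point holds in a limited form. The plan lists 6MWD among the outcomes of a phone-only follow-up while its only described method is a physical walk by inpatients. Followed as written, post-discharge 6MWD would be missing or an unstandardized self-report, and would not validly measure exercise tolerance. This touches one of the three follow-up measures, within one secondary outcome. It is worth correcting before the outcome is analysed or reported, but it does not threaten the primary result.

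The conclusion assumes that no post-discharge walking procedure exists beyond what the text describes. The content of Figure 2 (the schedule of assessments) was not available for this check; an in-person visit marked there would conflict with the three sections quoted and would need reconciling with them. The count of 2,448 is a ceiling that assumes every patient answers every call.

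**What to change.** Delete 6MWD from the telephone follow-up in Sections 2.9, 2.11 and 2.14, and name CAT and mMRC as the only phone outcomes. In Section 2.14, describe 6MWD as a test performed and not as a scale completed. Base the exercise-tolerance outcome on the in-hospital 6MWD, which is already collected daily. The choice of analysis day and any baseline adjustment are separate matters that this correction does not require.

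The cost is a change of wording, a protocol amendment to the Ethics Committee (Section 2.1), and the loss of post-discharge exercise data that the calls could not validly supply. If the sponsor wants such data, the alternative is to measure 6MWD in person after discharge under the same standard, at the cost of added visits.
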